## Abstract

**Background:**

Filgotinib was approved in Germany for treating patients with moderate to severe active ulcerative colitis in November 2021. It represents a preferential Janus kinase 1 inhibitor. The FilgoColitis study began recruiting immediately after approval and aims to assess filgotinib effectiveness under real-world conditions with a particular focus on patient-reported outcomes (PROs). The novelty of the study design is the optional inclusion of 2 innovative wearables, which could provide a new layer of patient-derived data.

**Objective:**

The study investigates quality of life (QoL) and psychosocial well-being of patients with active ulcerative colitis during long-term exposure to filgotinib. PROs related to QoL and psychometric profiles (fatigue and depression) are collected alongside with disease activity symptom scores. We aim to evaluate physical activity patterns collected by wearables as an addition to traditional PROs, patient-reported health status, and QoL in different phases of disease activity.

**Methods:**

This is a prospective, single-arm, multicentric, noninterventional, observational study with a sample size of 250 patients. QoL is assessed with validated questionnaires: the Short Inflammatory Bowel Disease Questionnaire (sIBDQ) for the disease-specific QoL, the EQ-5D for the general QoL, and the fatigue questionnaire (Inflammatory Bowel Disease-Fatigue [IBD-F]). Physical activity data are collected from patients using wearables (SENS motion leg sensor [accelerometry] and smartwatch, GARMIN vívosmart 4).

**Results:**

The enrollment started in December 2021 and was still open at the date of submission. After 6 months of study initiation, 69 patients were enrolled. The study is expected to be completed in June 2026.

**Conclusions:**

Real-world data for novel drugs are important to assess effectiveness outside of highly selected populations represented by randomized controlled trials. We examine whether patients’ QoL and other PROs can be supplemented with physical activity patterns measured objectively. Use of wearables with newly defined outcomes represents an additional observational tool for monitoring disease activity in patients with inflammatory bowel disease.

**Trial Registration:**

German Clinical Trials Register DRKS00027327; https://drks.de/search/en/trial/DRKS00027327

**International Registered Report Identifier (IRRID):**

DERR1-10.2196/42574

## Introduction

### Background

Ulcerative colitis (UC) is a chronic disease, which affects the digestive system and therefore, belongs to inflammatory bowel diseases (IBDs). Worldwide, more than 1.8 billion patients have been diagnosed with UC [1] with an ever-increasing trend [2,3].

UC has a chronic recurrent course of disease. Patients with UC have recurrent diarrhea, abdominal pain, nausea, weakness, or anemia, among other symptoms. As a result, the patients’ quality of life (QoL) and well-being can be impaired [4,5].

Currently, there are already many targeted therapies for moderate to severe UC. The use of biologics and other small molecules in patients with UC is increasing. Nevertheless, effectiveness is only approximately 30%. Recently, new modes of action have been introduced. In 2019, tofacitinib became the first Janus kinase (JAK) inhibitor approved in UC. However, as a pan JAK inhibitor, it has elicited some serious adverse events. Due to several Dear Doctor Letters (Rote-Hand-Brief), its acceptance by physicians has declined. Filgotinib is the first oral preferential JAK1 inhibitor, with fewer side effects expected than with a pan JAK inhibitor, approved for UC in Europe as of November 2021. Because pivotal studies with narrow predefined inclusion criteria do not always reflect treatment in routine clinical practice, the FilgoColitis study was established to reflect use under real-world conditions.

The novelty of the study design is the optional inclusion of 2 innovative wearables, which could provide a new layer of patient-derived data. Correlations with disease activity and QoL have been established before [6-8], but the cohort sizes were small and not in a longitudinal setting around targeted therapy. Therefore, real-world studies to assess the effect of digital health tools on disease activity are still needed [9].

### Objectives

This study aims to investigate the QoL and psychosocial well-being of patients with UC on filgotinib therapy over the long-term course of different disease phases under routine conditions. Therefore, we aim to use wearables additionally and collect patient-reported outcomes (PROs) related to QoL and psychomotor profiles (fatigue and depression), including physical activity, under real-world conditions.

Using wearables, we aim to investigate whether physical activity data are related to QoL in patients with UC and whether there is an association between physical activity patterns, health status, and QoL, and additionally to define a new outcome in UC treatment. Furthermore, we will evaluate the safety profile of filgotinib therapy considering (serious) adverse events.

## Methods

### Study Design

The FilgoColitis study is a prospective, single-arm, multicentric, investigator-initiated, noninterventional observational study.

### Outcomes

#### Primary Outcome Measure

The disease-specific QoL of patients with UC during long-term course of therapy is the primary outcome and is assessed with the help of the validated and internationally widely applied Short Inflammatory Bowel Disease Questionnaire (sIBDQ, German version), which contains 4 domains: bowel symptoms, emotional health, systemic systems, and social function [10]. Thereby, the different disease phases will be considered and examined.

#### Secondary Outcome Measures

As a secondary outcome, the safety profile of the filgotinib treatment will be explored, taking (serious) adverse events into account. Furthermore, clinical parameters such as the disease activity using the partial Mayo Score (pMayo, and additionally PRO2) and the Montreal Classification are assessed. In addition, the therapy deemed necessary and useful for the patient by the physician is recorded. The general QoL using the validated questionnaire EQ-5D-5L (which essentially consists of 2 pages: the EQ-5D descriptive system and the EQ visual analog scale [EQ-VAS]) is documented. The descriptive system comprises 5 dimensions: mobility, self-care, usual activities, pain or discomfort, and anxiety or depression. Each dimension has 5 levels: no problems, slight problems, moderate problems, severe problems, and extreme problems [11].

Fatigue is highly prevalent among patients with IBD [12]; therefore, the fatigue questionnaire (Inflammatory Bowel Disease-Fatigue [IBD-F]) is used in the study [13]. The scale of the IBD-F questionnaire was developed to be used for the diagnosis of fatigue or monitoring fatigue levels over time. The German version of the questionnaire has been published recently [14].

#### Additional Exploratory Outcome Measures

Wearables will be given to patients to collect their physical activity data, such as the number of steps per day, pulse rate, calories burned per day, physical activity patterns (day and night), stress, sleep rhythm, and sleep quality. We aim to examine the correlation between physical activity, stress, sleep, disease phases, and the patients’ psychosocial impairment. The used wearables are (1) an accelerometry-based sensor (SENS motion, Class 1M medical device), which is attached to the thigh of one leg, and (2) a smartwatch (GARMIN vívosmart 4). The wearables are adapted for German server–based documentation of the physical activity parameters (number of steps per day and speed), pulse rate, calories per day, physical activity patterns (day and night), rhythm and quality of sleep, and stress level.

### Statistics

#### Overview

This study is descriptive, and no formal hypotheses are tested. Patient and clinical characteristics are described to capture the baseline situation of patients treated with filgotinib. Descriptive statistics are used to summarize patients’ demographics and baseline data. Specifically, for continuous variables, the mean, 95% CI for the mean, SD, median, and IQR are reported. For discrete variables, the frequency and number of missing observations are reported.

In this noncomparative observational study, the primary end point is analyzed as the mean change (the difference in scores between the 2 time points) in sIBDQ values from baseline to week 10 and is presented along with the 95% CI. For sIBDQ scores (total), mean changes from baseline to week 10 (week 52 and week 104) are calculated with a 1-sample *t* test for differences between paired observations (or a nonparametric analog).

Patients’ sIBDQ QoL is summarized and compared concerning the following: (1) mean change from baseline to assessment points during the study and (2) at each analysis time point, the number of patients who have completed the questionnaire is reported as a percentage of eligible patients. Data will be collected at visit 1 (ie, at baseline) and then at approximately week 10, and every 6 months up to 2 years.

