#### Repeated Measurements Over Time

Each subject is assumed to have his or her mean response curve that explains how the sIBDQ score changes over time (intraindividual changes). A mixed effects model is used to model individual sIBDQ response curves over time.

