#### Justification of Sample Size

The difference in sIBDQ scores from baseline to week 10 (week 52 and week 104) will be analyzed. The null hypothesis is that the average difference is zero. The alternative hypothesis is that the average difference has a nonzero value. Based on the results of a previous study [15], we aim to demonstrate a difference of 7 points or more with an α of .05, assuming an SD of 12, and assuming that each pair of measurements on the same individual correlates with approximately 0.5. With a sample size of 250 subjects, a power of >90% is achieved to detect the above mean of paired differences with a 2-tailed paired *t* test [16].

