### Schedule of Visits

Visits at the study site are scheduled at inclusion (baseline visit week 0) and during follow-up (week 10, month 6, 12, 18, and 24). Follow-up visits are not fixed scheduled visits but are to occur when the study participant sees his or her physician as part of routine treatment.

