#### End of Patient Participation

The observation of each patient ends according to the schedule with the last study visit (month 24), after 2 years. A patient’s participation in the study will be terminated prematurely if at least one of the following criteria is met: (1) withdrawal of informed consent or death of the patient, (2) change of diagnosis, (3) lack of medical justification for further participation in the study, (4) premature termination of the complete study, or (5) subsequent discovery that not all inclusion criteria are met or that any exclusion criteria are met at baseline. A change in therapy does not result in study dropout. Furthermore, patients may be declared as lost-to-follow-up if they are no longer available and thus could not be documented at more than 2 consecutive visits.

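### The week 52 and week 104 sIBDQ changes come from paired t tests on patients seen at that visit, and may be biased in either direction; the mixed model already planned is the better source

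*Protocol article*

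**What the plan says.** In the protocol article, under Statistics, Overview, the primary end point is the average sIBDQ change between baseline and week 10, reported with a 95% CI. The same paragraph extends the method to the later time points: "mean changes from baseline to week 10 (week 52 and week 104) are calculated with a 1-sample" t test. Its object is given in the same sentence, which makes it a "test for differences between paired observations (or a nonparametric analog"). It also provides that "the number of patients who have completed the questionnaire is reported as a percentage of eligible patients" at each analysis time point.

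The next section, Repeated Measurements Over Time, adds a second analysis: "A mixed effects model is used to model individual sIBDQ response curves over time". It does not say that this model supplies the reported changes at weeks 52 and 104.

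On follow-up, Schedule of Visits states: "Follow-up visits are not fixed scheduled visits but are to occur when the study participant sees his or her physician" in routine treatment. End of Patient Participation lists withdrawal of consent, death and other reasons for early termination, and allows a patient to be declared lost if he or she "could not be documented at more than 2 consecutive visits". It also keeps patients under observation after a change of therapy.

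**The concern.** A paired difference needs both scores. A patient with scores at baseline, week 10 and months 6, 12 and 18 but none at month 24 is absent from the week 104 estimate. The paired mean then describes those who attended. It equals the mean for all enrolled patients only if attendance is unrelated to the change.

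That condition is doubtful here. Attendance follows routine care, and withdrawal or loss can relate to how the patient is doing. The later time points also matter: the Primary Outcome Measure section describes quality of life over the long-term course of therapy, and Strengths and Limitations says that improvement or worsening can be evaluated for all participants without bias from health status. A paired test limited to attenders does not secure that. The plan already contains a method that uses every recorded score, but it assigns the long-term changes to the one that does not.

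**Working it through.** **Inputs from the article (Justification of Sample Size).** "we aim to demonstrate a difference of 7 points or more with an α of .05, assuming an SD of 12", correlation about 0.5 between paired measurements, 250 patients, two-tailed paired t test, stated power above 90%.

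**The plan's own figure.** SD of the difference = 12 × √(2 × (1 − 0.5)) = 12. Power ≈ Φ(7 / (12/√250) − 1.96) = Φ(9.22 − 1.96) = Φ(7.26), which is above 99.99%. The stated figure is met; 33 pairs already give 90%. With 20%, 40% or 60% missing (200, 150 or 100 pairs) power stays above 99.9%. Lost patients therefore do not threaten power. The question is bias.

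**Yardstick.** 95% CI half-width = 1.96 × 12/√n: 1.7 points with 200 pairs, 1.9 with 150.

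**Simulation.** Six visits (baseline, week 10, months 6, 12, 18, 24), 250 patients, SD 12, correlation 0.5 between all visits, true change 7 at every follow-up visit, 200 runs per scenario (Monte Carlo standard error at most 0.08).

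*Assumed, because the article gives no figures:* permanent drop-out starting after week 10, reaching 20% or 40% by month 24. The log-odds of leaving at each visit shift by 0.5 to 2 for each 12 points of poorer change; a slope of −1 means that good responders leave. Loss depends on the last recorded change (missing at random, MAR) or on the current, unseen change (missing not at random, MNAR). The comparator is a likelihood-based repeated-measures model with free visit means and unstructured covariance.

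Month-24 mean change (truth 7.0):

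| Who leaves | Paired, 20% lost | Model, 20% lost | Paired, 40% lost | Model, 40% lost |
|---|---|---|---|---|
| Unrelated to response | 7.1 | 7.1 | 7.1 | 7.0 |
| Poor responders, MAR | 7.7 to 8.8 | 6.9 to 7.0 | 8.3 to 10.5 | 6.9 to 7.0 |
| Good responders, MAR | 5.9 | 7.1 | 4.6 | 7.1 |
| Poor responders, MNAR | 7.7 to 9.3 | 7.2 to 8.0 | 8.8 to 11.5 | 7.7 to 9.3 |
| Good responders, MNAR | 5.5 | 6.4 | 4.0 | 5.7 |

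At month 12 the pattern is the same but smaller. Under MAR with poor responders leaving, the paired mean is 7.3 to 8.0 (20% lost by month 24) or 7.7 to 9.2 (40%), and the model gives 6.9 to 7.1.

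With poor responders leaving under MAR, the month-24 paired bias is thus +0.7 to +1.8 against a half-width of 1.7, or +1.3 to +3.5 against 1.9. With good responders leaving under MAR it is 5.9 − 7 = −1.1 or 4.6 − 7 = −2.4.

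**Form of time in the model.** Suppose the true change is 0 at baseline and 7 at each later visit, and a straight line is fitted to complete data at weeks 0, 10, 26, 52, 78 and 104. The mean week is 270/6 = 45. Sxx = 20,380 − 6 × 45² = 8,230. Sxy = 7 × (270 − 5 × 45) = 315. The slope is 315/8,230 = 0.038 per week, so the fitted change is 0.4 at week 10 and 4.0 at week 104, against a true 7. A model with linear time could do more harm than the paired test.

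**The case against.** **The direction is not known.** A reader might infer that the long-term gain will be overstated because those who do well stay. The documents do not support that. They give no drop-out rate or mechanism. Visits tied to routine care can work the other way, since unwell patients may be seen more and well patients may skip visits. A change of therapy does not end participation, so treatment failure alone removes nobody. This stands: bias is possible, but its sign and size are unknown.

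**The mixed model is not a cure.** A reader might infer that it avoids the problem. It does so only under MAR and with a suitable form for time. Under MNAR it remains off, although closer to the truth than the paired mean in each MNAR scenario above. This stands too.

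**Week 10.** A reader might extend the point to the primary end point. The simulation has no drop-out before week 10, so it shows no bias there and is no evidence of any. Attrition over ten weeks is likely to matter less, and the sample size rests on the paired test. There is no case here for changing that analysis.

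**The loss-to-follow-up rule.** A reader might infer that it adds to the bias. It needs at least three consecutive missed visits, and after month 12 only months 18 and 24 remain, so a patient last seen at month 12 or later cannot meet it. The count is right, but the label decides neither which pairs enter the t test nor the estimate.

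**Already partly handled.** The study is descriptive, and completion percentages will show how much is missing. That discloses attrition but does not correct for it. Further missing-data handling may sit in the full protocol or SAP, and its absence from an article is no finding. The point rests on the method that the article does state.

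**Conclusion.** The point holds for weeks 52 and 104. The stated paired tests use only patients with a score at that visit and are unbiased only if missingness is unrelated to the change. Under the assumed drop-out of 20% to 40%, a true 7-point change at month 24 would be reported as anything from 7.7 to 10.5 if poor responders leave under MAR, or as 5.9 down to 4.6 if good responders leave. Such an error can match or exceed the CI half-width of 1.7 to 1.9 points, though at the milder settings it is smaller. The likelihood model gives 6.9 to 7.1 under MAR, but is still 0.2 to 2.3 points high when loss of poor responders depends on unseen scores.

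The SD, correlation and effect are the plan's own. The drop-out rates, slopes and mechanisms are assumptions, so the figures show what could happen and do not predict it. The week 10 primary end point is not called into question. The change is worth making before analysis.

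**What to change.** - Take the week 52 and week 104 mean changes and their 95% CIs from the mixed model already planned, fitted to every patient with at least one sIBDQ score.
- Enter visit as a categorical effect. If actual visit dates are used, because visits are not fixed, specify a flexible function of time and not a straight line.
- Keep the paired t test at weeks 52 and 104 as a supportive analysis.
- Keep the week 10 primary analysis as planned.
- Add a sensitivity analysis for data missing not at random, for example by shifting the unseen scores of patients who left over a stated range in both directions.

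The cost is some wording in the analysis plan and a little more analysis work; no new data are needed. The main estimates at weeks 52 and 104 would then rely on missing at random. That is still an assumption, but weaker than the one the paired test needs, and the sensitivity analysis shows how much depends on it.

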### Definition of the Study Population

This prospective observational investigator-initiated trial will be conducted with 250 participants at approximately 50 sites all over Germany. The gender ratio will be balanced.

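### The primary 95% CI treats 250 patients from about 50 sites as independent; if sIBDQ changes correlate within site, it is modestly too narrow

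*Protocol article*

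**What the plan says.** For week 10, the Statistics Overview in the protocol article states that "the primary end point is analyzed as the mean change (the difference in scores between the 2 time points) in sIBDQ values from baseline to" that visit, and the estimate is shown with its 95% CI. It names the calculation: a one-sample *t* "test for differences between paired observations (or a nonparametric analog". The same paragraph applies it to weeks 52 and 104. The section opens with "This study is descriptive, and no formal hypotheses are tested".

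The Definition of the Study Population says the study "will be conducted with 250 participants at approximately 50 sites all over Germany".

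Repeated Measurements Over Time adds a mixed effects model, described only in terms of each patient's own sIBDQ curve. Justification of Sample Size uses a two-tailed paired *t* test. Neither section mentions site.

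Under Patient Identification, each patient number begins with a 3-digit clinic number, so site is recorded for every patient.

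**The concern.** A one-sample *t* interval on paired differences is exact in its logic only if the differences are independent between patients. Here patients are grouped in about 50 hospitals and practices. There is one arm, so no comparison within sites removes a shared site effect on change. Any such effect adds to the variance of the overall mean, and the *t* interval does not count it.

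The end point is a change, so stable site differences in score level drop out: a site whose patients always score low, or that always handles the questionnaire in one way, contributes nothing. Only site differences in the amount of change matter. The article describes several features that could produce them:

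- Follow-up takes place at routine appointments rather than on fixed dates (Schedule of Visits), so the real timing of week 10 can differ by site.
- A switch of therapy does not end participation (End of Patient Participation), so local treatment practice can enter the outcome.
- Staff help patients with the questionnaires (Strengths and Limitations). If that help changes between visits, it can affect the change score.

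Because the study is presented as descriptive, the estimate and its interval are the main product. What is at stake is whether the nominal 95% interval covers at 95%, not whether an effect is detected.

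**Working it through.** **Inputs from the article.** N = 250 and about 50 sites (Definition of the Study Population), so the mean site size is m = 250/50 = 5. From Justification of Sample Size: "we aim to demonstrate a difference of 7 points or more with an α of .05, assuming an SD of 12". That section also puts the correlation between a patient's two scores at about 0.5.

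**Inputs assumed.** ICC of the change score 0.02 to 0.05, and CV of site size 0 (equal sites) or 1 (very uneven recruitment). The article gives none of these.

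**Step 1: the plan's own figure.** If 12 is the SD of a single score, the SD of the difference is √(2 × 12² × (1 − 0.5)) = 12. If 12 is already the SD of the difference, the value is the same. The standard error is 12/√250 = 0.759, and 7/0.759 = 9.22. Power is Φ(9.22 − 1.96), essentially 100%. The stated power above 90% is reproduced with a wide margin; about 33 pairs would already give 90%.

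**Step 2: unadjusted interval.** The half-width is 1.9695 × 0.759 = 1.49 points (249 degrees of freedom, all 250 patients contributing).

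**Step 3: clustering.** Design effect DE = 1 + ((1 + CV²) × m − 1) × ICC. The standard error and the half-width are multiplied by √DE. The true coverage of the unadjusted interval is about 2Φ(1.96/√DE) − 1.

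| CV | ICC | DE | √DE | Half-width | Coverage of the plain interval |
|---|---|---|---|---|---|
| any | 0 | 1.00 | 1.00 | 1.49 | 95.0% |
| 0 | 0.02 | 1 + 4 × 0.02 = 1.08 | 1.04 | 1.55 | 94.1% |
| 0 | 0.05 | 1 + 4 × 0.05 = 1.20 | 1.10 | 1.64 | 92.6% |
| 1 | 0.02 | 1 + 9 × 0.02 = 1.18 | 1.09 | 1.62 | 92.9% |
| 1 | 0.05 | 1 + 9 × 0.05 = 1.45 | 1.20 | 1.80 | 89.6% |

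**Step 4: power under clustering.** In the last row the effective sample size is 250/1.45 = 172.4. The standard error is 12/√172.4 = 0.914, and 7/0.914 = 7.66. Power is Φ(7.66 − 1.96), still above 99.9%.

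**Step 5: would a site intercept in the planned mixed model be enough?** Write the score at visit *t* as visit mean + site effect + patient effect + error. Subtracting baseline from week 10 removes the site effect, because it is the same at both visits. The standard error of the change therefore stays at 0.759 whatever the site-intercept variance. A numerical check with 50 sites of 5 patients gave 0.759 for site-intercept variances of 1, 7, 14 and 50. Only a site effect on the change itself alters the interval.

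**The case against.** The strongest objection is that this is a journal article and that site terms and variance estimators usually belong in the full protocol or SAP, neither of which is shown. That holds for the mixed model, which gets one sentence, and it would be wrong to conclude that the full plan ignores site. It holds less well for the primary interval: the article is not silent there but names a specific calculation, and that calculation assumes independence.

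A reader might infer that the interval is too narrow as a matter of fact. The documents do not support this. It requires a positive ICC of change, no such figure is given, and at an ICC of 0 the interval is valid. Subtracting baseline also makes the relevant ICC an ICC of change, not of score level.

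A reader might also infer that the article claims more precision than the design delivers. It states no interval width or precision target; the 1.49 points above is derived here from the sample-size inputs.

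Nor does the point threaten the sample size. On these assumptions the half-width grows by 0.06 to 0.31 points against a 7-point difference, and power is untouched.

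Finally, sites are chosen by the investigators (Selection of Study Sites) rather than sampled, so treating site as random is partly a choice of inference. However, Justification for Study Design presents the choice of sites as a route to results that represent the wider population, and that favours counting variation between sites.

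**Conclusion.** The point stands in conditional form and is minor. The named primary method assumes independent patients while the design groups them in about 50 sites. If changes correlate within site, the 95% CI is modestly too narrow: by 4-10% in standard error with equal sites and by 9-20% with a site-size CV of 1, for an ICC of 0.02 to 0.05. The least favourable of these cases brings true coverage to about 90%. The result rests on an assumed ICC and CV, on an SD of the difference of 12, and on all 250 patients contributing. No conclusion about a 7-point change depends on it.

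**What to change.** Compute the primary 95% CI for the mean change with a site-clustered standard error, taking site from the clinic number in the patient identifier. This keeps the point estimate as the plain mean over patients. An alternative is a model of the change score with a site random intercept or, equivalently for the change from baseline to week 10, a random site-by-time effect in the longitudinal model. With unequal sites these models weight patients differently from the plain mean, so the choice should be stated in advance. Do not rely on a site random intercept alone in the model of scores over time. Reporting the estimated ICC of change would show whether the adjustment mattered.

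The cost is one sentence in the analysis plan and no new data. The downside is a slightly wider interval. If degrees of freedom are taken from the number of sites (49 for 50 sites), the half-width is 1.53 rather than 1.49 even at an ICC of 0.
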